## Abstract

**Background:**

*Staphylococcus aureus* is a frequent colonizer of the human skin and mucous membranes but can also cause a variety of serious infections. Antimicrobial resistance is an increasing worldwide challenge and is mainly driven by an overuse of antimicrobials*.* To avoid the spread of methicillin-resistant *Staphylococcus aureus* (MRSA) in Denmark, the Danish Health Authority recommends decolonization treatment of MRSA carriers and their household contacts. Standard decolonization treatment includes chlorhexidine body wash and mupirocin nasal ointment, especially throat carriage is difficult to treat. The broad-spectrum antibiotic, clindamycin, is often added to the decolonization treatment, but there is currently low scientific evidence for this treatment.

**Aim:**

To investigate whether the addition of clindamycin to the standard decolonization treatment increases decolonization success in MRSA throat carriers.

**Methods:**

A randomized, placebo-controlled, double-blinded trial, including patients ≥ 18 years, who tested MRSA positive in the throat after completing one standard decolonization treatment. All carriers included in the trial receive standard decolonization treatment and are randomized to treatment with either placebo or clindamycin capsules for 10 days. We plan to include 40 participants in each of the two treatment arms.

**Discussion:**

Due to the lack of consistent scientific evidence of clindamycin’s effect in MRSA decolonization and the worldwide urgent need to reduce the use of antibiotics, we judged that a 30% increase in the decolonization success rate in carriers treated with clindamycin is appropriate to justify prescribing clindamycin as part of the decolonization treatment of asymptomatic MRSA carriers.

**Trial registration:**

EudraCT number 2019-002631-29

**Supplementary Information:**

The online version contains supplementary material available at 10.1186/s13063-022-06443-1.

## Administrative information

Note: The numbers in curly brackets in this protocol refer to SPIRIT checklist item numbers. The order of the items has been modified to group similar items (see http://www.equator-network.org/reporting-guidelines/spirit-2013-statement-defining-standard-protocol-items-for-clinical-trials/).

## Background and rationale {6a}

*Staphylococcus aureus* (*S. aureus*) frequently colonizes the human skin and mucous membranes. Longitudinal studies usually divide *S. aureus* carriers into either persistent or intermittent carriers, but because the number of samplings, follow-up periods, and study populations differ between studies, the designation of carrier state is inconsistent [1]. It has been estimated that around 20% of the population are persistent carriers, 60% are intermittent carriers, and 20% are non-carriers [2]. *S. aureus* is an opportunistic pathogen that can become invasive and cause a large spectrum of infections. *S. aureus* is frequently the cause of skin and soft tissue infections, e.g., wounds, furuncles, and abscesses, but can also cause arthritis, osteomyelitis, and endocarditis and is a common pathogen in surgical site infections and in infections related to foreign bodies, such as catheters and prosthetic devices [3].

Antimicrobial resistance is an increasing challenge worldwide. The first methicillin-resistant *Staphylococcus aureus* (MRSA) were seen in 1961 just 1 year after the antibiotic methicillin was introduced [4]. For several decades, MRSA was mainly hospital-associated, but since the mid-1990s, it has become increasingly prevalent in the community where it often affects children and younger adults [5, 6]. MRSA can cause the same types of infections as methicillin-susceptible *S. aureus*, but often only colonizes the skin and mucus membranes. MRSA carriers are at risk of developing infections [7] as well as to transmit MRSA to others. National guidelines on how to treat MRSA carriage are available in some countries, but the approach often differs between countries. The Danish Health Authority has published a national guideline on how to prevent the spread of MRSA to keep the prevalence of MRSA low in Denmark [8]. Laboratory findings of MRSA are routinely reported to the Danish Patient Safety Authority and the national reference laboratory, Statens Serum Institut, in order to monitor the MRSA prevalence in Denmark and identify outbreaks [9]. The guideline recommends that MRSA carriers and their household members undergo a 5-day decolonization treatment regime, consisting of mupirocin 2% nasal ointment twice daily in both nostrils, daily full body wash with chlorhexidine 4% soap, and performs thorough cleaning of the home. Unfortunately, many carriers are still MRSA-positive after completing the treatment, and especially throat carriers are difficult to treat [5]. In case of treatment failure, a new treatment is often recommended. If the patient is a throat carrier, we sometimes add antibiotics to the standard treatment on the third decolonization attempt, clindamycin being the first-line choice in our region, as we hypothesize that the treatment is more effective when clindamycin is added. In a recently published retrospective study by our group describing the MRSA treatment data of 164 patients from Copenhagen [5], we found that throat carriers had a higher treatment failure rate, but adding clindamycin to the first decolonization treatment did not significantly increase the success rate. However, looking at the second decolonization treatment, our data (not published) showed that 57% of the throat carriers treated with clindamycin became MRSA-free compared to 29% of the throat carriers not receiving clindamycin, indicating that there might be an effect of adding clindamycin to the second treatment. We find it likely that the non-significant effect following the first treatment was partly due to many patients being intermittent carriers, and thus, the outcome of the first treatment is highly influenced by the spontaneous loss of MRSA. We consider patients that are still throat carriers after one decolonization treatment to be more permanent carriers with a lower chance of spontaneous loss influencing the treatment outcome. As we now rarely use clindamycin for the first decolonization treatment, but often for the second treatment in throat carriers, we decided to design a randomized controlled trial (RCT) testing the effect of adding clindamycin to MRSA throat carriers for their second decolonization treatment. To our knowledge, the only RCT examining non-infected/non-surgical MRSA carriers including clindamycin for treatment of MRSA carriage is a Swedish study that showed a significant effect of a standard treatment plus the antibiotic rifampicin in combination with either clindamycin or sulfamethoxazole/trimethoprim compared to the standard treatment alone in long-term MRSA carriers [10]. As most of our patients are healthy individuals without infections, adding systemic antibiotics to the decolonization treatment must be considered carefully. There is a risk of side effects in the individual patient, and in the era of a rising incidence of antimicrobial resistance, prudent use of antibiotics is crucial to avoid further selection of resistance [11].

As there are no published clinical trials evaluating the effect of clindamycin monotherapy for MRSA throat carriage, which has been the common practice for several years in our region, and we wish to avoid using rifampicin due to its side effects and interaction profile [12], we planned this randomized trial to fill in the gap in the literature {6b}.

### Objectives {7}

The objectives are to evaluate our current decolonization regime and test our hypothesis that decolonization treatment in combination with oral clindamycin is superior to standard treatment alone, at the second attempt of decolonization treatment.

### Outcomes {12}

The primary outcome is MRSA-negative swabs 1 month after completing the treatment.

The secondary outcome is MRSA-negative swabs 6 months after completing the treatment.

## Method and trial design {8}

This is a randomized, placebo-controlled, double-blinded trial, including patients ≥ 18 years of age who have tested MRSA-positive in their throat after completing one standard decolonization treatment. The protocol follows the SPIRIT reporting guidelines [13].

### MRSA patients

In the Capital Region of Denmark, the number of new MRSA-positive patients ≥ 18 years was 855 in 2018 with an estimated MRSA prevalence of < 0.5% [14, 15]. In around 60% of cases, MRSA is first found in a sample from an infection (mainly skin and soft tissue infections), and approximately 75% of these patients are MRSA carriers following the infection. Therefore, we expect to encounter approximately 700 newly diagnosed MRSA carriers per year of which around 66% are throat carriers in their first screening sample (462 patients). Based on retrospective data, around 40% become MRSA-free after the first decolonization treatment, which means that approximately 277 of the throat carriers ≥ 18 years old are still MRSA-positive after the first treatment. We expect that 40% of these patients have one or more exclusion criteria and therefore end up with approximately 330 patients that fulfill the inclusion criteria within the study period. As a part of our working routine, we automatically obtain information about all MRSA culture-positive samples in the lab on daily basis.

### Study settings and recruitment {9}{15}

Patients are recruited from the Capital Region via MRSA Knowledge Center Hvidovre Hospital or MRSA team, Herlev Hospital. Patients have since their first positive MRSA result an active connection to the MRSA Knowledge Center Hvidovre Hospital/MRSA team, Herlev Hospital. Patients often call for support, guidance, and treatment plans, and routine letters are often sent out to patients. When the department’s nurses or doctors have written or oral contact with an MRSA carrier that could be a possible candidate for the trial, the possibility of participating in the trial will be mentioned and the investigator’s contact details will be given.

When an eligible patient wishes to participate in the trial, oral and written consent is obtained by the investigator during a physical meeting at Hvidovre Hospital, and the participant receives a randomized decolonization package. The package includes study medicine, cleaning guide, participant information, booklet regarding rights as a study participant, and a diary to fill out daily during the study from days 1 to 14, asking about trial compliance and adverse events {32}. The investigator obtains signed informed consent (Fig. S1) and returned diaries in a secure locked room, at Hvidovre Hospital {26a}.

### Data collection plan {18a}

Participant data will be pseudonymized and will be handled according to the national rules and general data protection regulation (GDPR) {27}. A case report form (eCRF) is created for each patient for the collection of trial data using Research Electronic Data Capture (REDcap), a secure web application for managing online databases designed for non-commercial clinical research {19}. This will include the following data: project number, date of birth, age, sex, height, weight, body mass index (BMI), relevant medical history/current medication, sites and dates of MRSA-positive samples, prior MRSA decolonization treatments, household composition and household members MRSA carrier state, typing and resistance data of the MRSA strain, and laboratory and investigational results. For sexually active female participants of reproductive age, a pregnancy test is performed before enrollment, and we record the use of contraceptives. Auditing of data is performed by the GCP unit.

### Interventions {11a}

Participants are randomly allocated to receive a randomized, double-blinded {17a} decolonization package and are instructed to follow a standard 5-day cleaning regime as well as using mupirocin nasal ointment 2% and chlorhexidine body wash 4%. The treatment includes either placebo capsules to consume, 2 capsules three times daily for 10 days, or clindamycin 300-mg capsules, 2 capsules three times daily for 10 days. Placebo and clindamycin are manufactured to look exactly alike by Glostrup Pharmacy {16a/b/c}, who is also in charge of the randomization/blinding of the packages. Individual sealed and securely closed envelopes for each included participant ID have been created. An emergency unblinding procedure is established to allow the investigator the option to withdraw and unblind participants in case of an emergency {17b}.

### After the treatment

Thirty to 60 days after the end of treatment, the participants will routinely have MRSA control swabs taken by their general practitioner (GP) according to the national MRSA guidelines. Control swabs and the results of these are handled routinely. In laboratory settings, Eswabs (Copan) are inoculated in an enrichment broth containing 2.5% NaCl, 3.5 mg/L cefoxitin, and 20 mg/L aztreonam for overnight incubation at 35 °C. From the broth, 10 μL is spread on a 5% blood agar and an MRSA chrome agar (Biomérieux). Susceptibility testing is performed by disk diffusion using EUCAST breakpoints. MRSA-positive isolates are confirmed by an in-house PCR [16].

If the participant is MRSA-positive 1 month after the treatment, the participant will leave the trial, and the randomization will be unblinded in order to plan the most optimal treatment outside the trial, without revealing the given treatment to the investigator, leaving the investigator blinded until the end of the trial, approximately September 2025 (currently planned), when the final swab results from the last included participant have been analyzed (Table 1) {13}.

**Table 1 Tab1:** Schedule of enrollment, interventions, and assessments

	Enrolment and allocation of treatment	Post-treatment control swab	Post-treatment control swab*
**Timepoint/assessments**	***T***_**0**_	***T***_**1 month**_	***T***_**6 month**_
Enrollment	X		
Eligibility screen	X		
Informed consent	X		

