**Interventions**			
Standard decolonization + clindamycin	X	X	X
Standard decolonization + placebo	X	X	X

^*^If MRSA positive at *T*_1 month_, the participant leaves the trial and will not be sampled in the trial at *T*_6 month_

If MRSA-negative at 1 month, no unblinding will take place at this point. The participant will have new control swabs taken at the GP 6 to 8 months after completing the treatment, as generally recommended. If MRSA-negative at 6–8 months after treatment, the participant is declared MRSA-free according to the national MRSA guidelines.

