### Modifications {11b}

Participants will be informed that participation is voluntary and that they have the right to leave the study at any given time, without providing a reason, and with no loss of benefits concerning treatment outside the study. If a participant withdraws, we will be able to use the results that we have at the given time of the withdrawal, as mentioned in the handout information. The investigator has the right to terminate participation if considered in the best interest of a given participant.

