### Statistics {20a/b/c}

Continuous data are expressed as median and range. Power calculations are based on an expected proportion of 20.3% in the control group and a minimum relevant difference of 30% points resulting in an expected 50.3% in the intervention group. Power is set at 80 and significance level at 0.05%. Since only superiority is of interest, a one-tailed *p*-value will be used. The statistical software “R” [17] was used for power calculation. The analysis will be performed using Fisher’s exact test or chi-squared test depending on sample size. Statistical calculations will be performed using IBM SPSS Statistics, version 25, IBM Corporation, and other(s) 1989, 2018. We intend to include every study participant randomized in the primary analysis, only omitting excluded participants, where no data is available after randomization or in case of lack of compliance. Missing data will be excluded from the analysis. No subgroup or interim {21b} analysis is planned.

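### Read literally, the exit of 1-month positives and the exclusion of missing data limit the 6-month secondary outcome to 1-month negatives, which can hide or reverse a difference in sustained clearance

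*Protocol article*

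**What the plan says.** Outcomes {12} names one secondary outcome: "The secondary outcome is MRSA-negative swabs 6 months after completing the treatment". It gives no denominator.

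After the treatment sets the pathway: "If the participant is MRSA-positive 1 month after the treatment, the participant will leave the trial". Such participants are then managed elsewhere, and for that purpose the section says that "the randomization will be unblinded in order to plan the most optimal treatment outside the trial". The footnote to Table 1 repeats the exit: "the participant leaves the trial and will not be sampled in the trial at" 6 months. Only participants negative at 1 month go on to the control swab at 6 to 8 months. A negative result there is what declares them MRSA-free.

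Statistics {20a/b/c} gives one rule for incomplete data: "Missing data will be excluded from the analysis". Its statement on who is analysed refers to the primary analysis: "We intend to include every study participant randomized in the primary analysis, only omitting excluded participants", with omission for lack of any post-randomisation data or for non-compliance. Modifications {11b} adds: "If a participant withdraws, we will be able to use the results that we have at the given time of the withdrawal". No section says how a 1-month positive is to be counted at 6 months.

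**The concern.** Every 1-month positive lacks a 6-month swab by design. If that absent swab is treated as missing data, the participant drops out of the 6-month analysis and only 1-month negatives remain. Membership of that group is decided after randomisation by the primary outcome, which the plan expects to differ between arms by 30 percentage points. The two groups of responders are then not the randomised groups. The clindamycin responders would include people who cleared only because of the drug, while the placebo responders would be those who cleared on standard treatment alone.

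The result would describe persistence among responders, not the effect of adding clindamycin on clearance at 6 months. This is the only outcome in the plan that bears on lasting clearance.

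**Working it through.** **Inputs from the protocol article.** Statistics {20a/b/c}: "expected proportion of 20.3% in the control group and a minimum relevant difference of 30% points resulting in an expected 50.3% in the intervention group". The same section sets a one-sided test at 80% power, by Fisher's exact or chi-squared. Sample size {14}: 31 per group needed, 40 recruited, 9 per group expected to drop out or be non-compliant.

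**The plan's own figure.** Pooled normal approximation without continuity correction, one-sided 5%, mean proportion (0.203 + 0.503)/2 = 0.353:

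n = [1.645 × √(2 × 0.353 × 0.647) + 0.842 × √(0.203 × 0.797 + 0.503 × 0.497)]² / 0.30² ≈ 30.3, rounded up to 31.

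This matches the protocol, and power at 31 per group is 80.8%. The significance level is printed as 0.05%. Only 5% reproduces 31, since a literal 0.0005 would need 85 per group. The planning rates can therefore be carried forward.

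**Who would enter a responders-only comparison.**
- Of 31 per arm: 31 × 0.203 = 6.3 placebo and 31 × 0.503 = 15.6 clindamycin, so about 6 against 16.
- Of 40 per arm, if all were evaluable: 40 × 0.203 = 8.1 and 40 × 0.503 = 20.1, so about 8 against 20.

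**Two ways to compute the 6-month difference.** Let rP and rC be the proportions of 1-month negatives still negative at 6 months on placebo and clindamycin. The document gives neither, so the values below are assumptions.
- Responders only: rC − rP.
- 1-month positives counted as failures: 0.503 × rC − 0.203 × rP.

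| Assumed rP, rC | Responders only | Failures counted: placebo, clindamycin | Difference |
|---|---|---|---|
| 80%, 80% | 0 points | 16.2%, 40.2% | +24.0 points |
| 90%, 70% | −20 points | 18.3%, 35.2% | +16.9 points |
| 90%, 60% | −30 points | 18.3%, 30.2% | +11.9 points |
| 80%, 60% | −20 points | 16.2%, 30.2% | +13.9 points |
| 70%, 90% | +20 points | 14.2%, 45.3% | +31.1 points |

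With rP = 90%, the two differences have opposite signs whenever rC lies between 0.203 × 0.9 / 0.503 = 36% and 90%.

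**Power in the equal-retention case (80%, 80%).** By exact enumeration of the one-sided Fisher test at 5%, power is about 2% for 6 against 16 responders. It is about 59% for 31 against 31 with failures counted.

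**The case against.** The strongest reply is that a 1-month positive is not missing. The failure has been observed, the absent later swab is a planned exit, and a participant must pass the 1-month swab before being declared MRSA-free. On that reading the missing-data sentence covers only swabs that were due and not taken, and Modifications {11b} allows the 1-month result to be used. This reading is possible, and it stands to this extent: a reader might infer that the protocol prescribes a responders-only analysis, but it does not say so. The denominator is inferred from two rules. Yet exclusion is the only rule printed, the commitment to all randomised participants is tied to the primary analysis, and permission to use earlier results does not make a 1-month positive a 6-month failure.

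A second reply is that secondary denominators belong in an analysis plan, which is not shown. Silence alone would indeed be no finding. The point here is that two stated rules, applied together as written, give a misleading comparison.

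Third, the retention rates are assumed, and reversal requires placebo responders to hold clearance better than clindamycin responders. That is correct, and the last row of the table shows a case with no reversal. Masking, however, needs nothing more than equal retention.

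Fourth, a reader given both the 1-month and the 6-month counts could rebuild sustained clearance. That limits the harm if both are reported for the same population, but the planned test would still be run on the selected group.

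**Conclusion.** The point holds as a defect in how the secondary outcome is fixed. Taken literally, the rules compare about 6 placebo with 16 clindamycin responders (8 with 20 if all 40 per arm are evaluable). Under the assumed retention rates, a difference in sustained clearance of +24 points would appear as 0, and differences of about +17 or +12 points would appear as −20 or −30. These sizes depend on the protocol's planning rates at 1 month and on retention rates that the document does not supply. They show what can happen and are not forecasts.

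Two further inferences should not be drawn. The primary 1-month outcome and the 31 per group are not affected, because the exit rule acts only after the 1-month result. Nor is the failure-counted figure the true carriage difference at 6 months. Participants positive at 1 month are treated outside the trial and not swabbed within it, so their later carriage is unknown. The figure measures sustained clearance, and under equal 80% retention it is simply 0.8 × 30 = 24 points.

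**What to change.** - Define the secondary outcome as MRSA-negative at both the 1-month and the 6-8 month control swabs. Analyse it by randomised arm with 1-month positives counted as failures.
- Use all randomised participants as the denominator, or at least the same population as the primary analysis. The primary set omits non-compliant participants and those with no post-randomisation data, so state which is used and acknowledge any difference between the two outcomes.
- State that the missing-data rule applies only to swabs that were due but not obtained, at 1 month or at 6-8 months. Report their number per arm, with a sensitivity analysis counting them as failures.
- Report persistence among 1-month negatives as descriptive only.

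The cost is a documented amendment to a trial that has been recruiting since May 2020. It should be made before the trial is unblinded for analysis, so that the choice of denominator cannot follow the result. It also commits the trial to a composite estimand, sustained clearance, in place of carriage at a single time point. No extra swabs and no change to clinical management are needed.
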